**Abstract**

This proposal, which focuses on the effects of a readily translatable and attainable dietary lifestyle intervention for aged individuals (time restricted eating [TRE]) against age-related microvascular endothelial dysfunction, is a rational avenue to investigate the effects of modifiable lifestyle interventions to ameliorate cognition and health-span in the Oklahoma elderly population. Caloric restriction (CR) exerts multifaceted anti-aging and lifespan extending effects and has been demonstrated to be an effective nutritional intervention that can improve vascular health and cognitive function. However, adherence to CR remains a challenge and a translational barrier as most humans may not be able or willing to reduce their caloric intake by 30% over extensive periods of time. Intermittent fasting can recapitulate the benefits of CR without limiting calorie intake in older adults. TRE is considered the best approach to intermittent fasting for elderly individuals as it allows consumption of required calories within a condensed daily eating window (4 to 10 hours), resulting in the greatest fasting stimulus without a net reduction in calorie intake. Guided by our published results and strong preliminary data, we propose to elucidate the role of TRE in aging-induced impairment of NVC responses and dysregulation of CBF, offering new targets for prevention and treatment of age-related vascular cognitive impairment and related dementias. To test our hypothesis, we propose the following specific aims: 1) Determine the impact of TRE on microvascular endothelial function, cognitive function, and NVC responses and microvascular endothelial in healthy adults, and 2) Determine the impact of TRE on circulating biomarkers and cerebrovascular endothelial cell SIRT1 activity. Our expectation is that our findings will provide background for novel therapeutic approaches for prevention/treatment of cognitive impairment in high-risk elderly patients.

**A. Specific Aims**

Our central hypothesis is that closer adherence to TRE will improve endothelial function, NVC responses, resulting in improved cognitive performance, potentially through activation of SIRT1-dependent vasoprotective pathways. The following aims are proposed:

**Aim 1: Determine the impact of TRE on microvascular endothelial function, cognitive function, and NVC responses in older adults.** Study 1 will evaluate NVC responses using functional near-infrared spectroscopy (fNIRS), electroencephalography (EEG), and dynamic retinal vessel analysis (DVA). Study 2 will evaluate peripheral micro- and macrovascular endothelial function using laser speckle contrast imaging and flow-mediated dilation approaches. Study 3 will evaluate performance in different cognitive domains using a comprehensive battery of cognitive tests.

**Aim 2: Determine the impact of TRE on circulating biomarkers and cerebrovascular endothelial cell SIRT1 activity.** Irrespective of whether the results of Aim 1 are positive or negative, we need to understand the effect of TRE on SIRT1 activity levels and related deacetylation by-products in the human participants. Study 4 To assess the effects of TRE on cellular SIRT1 activity we will treat human cerebral microvascular endothelial cells (CMVECs) with fasting serum obtained from older adults undergoing TRE and age-matched controls. We anticipate that altered SIRT1 activation will affect NO bioavailability, endothelial oxidative stress, and inflammation in CMVECs and in circulating blood. We also hypothesize that these changes will correlate the magnitude of NVC impairment and cognitive performance in older adults, and that TRF treatment I will improve these outcomes.

**B. Background and Significance**

As life expectancy rises, VCID has become a leading public health issue in the developed countries. VCID is the second most common cause of dementia after Alzheimer's disease (AD), and accounts for close to 50% of cognitive impairment cases in the elderly [1]. Additionally, vascular contributions to cognitive impairment and dementia are now considered critical for AD as well. There is strong clinical evidence that impaired blood supply to the brain plays a critical role in cognitive decline in the elderly [2-7]. The clinical findings of aging-induced dysregulation of CBF and cognitive impairment have also been confirmed in animal models (Fig 2) [8-12]. To date, no interventional strategies exist for the prevention or treatment of aging induced CBF dysregulation and cognitive decline. Because the energetic demands of neurons are high and the brain has little reserve capacity, maintenance of normal brain function is critically dependent on moment-to-moment adjustment of CBF [13-16]. This requirement is fulfilled by NVC, a vital mechanism that maintains an optimal cerebral tissue microenvironment, enabling rapid increases in O2 and glucose delivery and washout of toxic metabolites during periods of intense neuronal activity. Aging results in significant impairment of cerebrovascular endothelial function, which promotes NVC dysfunction which are causally linked to the genesis of cognitive decline [13, 17, 18]. It is believed that TRE mimics several aspects of the beneficial biological effects of calorie restriction [19]. Importantly, TRE can improve endothelial function. Our contribution is expected to be a demonstration that TRE confers endothelial rejuvenating effects in the cerebral microcirculation by inducing SIRT1-dependent pathways, which results in restoration of NVC responses and increased CBF. TRE-mediated cerebrovascular geroprotection is expected to improve cognitive function in aging.

**C. Preliminary Studies/Progress Report**

Currently, there is not pilot results from human participants.

**D. Research Design and Methods**

**Clinical trial design:** We will test the primary hypothesis that TRE improves NVC responses and endothelial function in older adults. This hypothesis will be tested by assessing the effects of TRE (10 hours eating window) in community dwelling older adults (55-80 years of age) in a 6-month study. At screening (Visit 0), participants will be evaluated for eligibility criteria, after obtaining informed consent. Individuals

will be asked report medications or supplements intake. Screening assessments and baseline physiological assessments may be conducted at that same visit (baseline, Visit 1) if all eligibility criteria are met, or within 4 weeks of Visit 0 (screening window) at the discretion of the investigator, when eligibility will be again confirmed. After baseline, the first fMRI and dual X-ray absorptiometry (DXA) scan visits will be performed, if the participant opts in to these measurements.

Upon completion of baseline physiologic measurements, all participants will be instructed to maintain TRE for the ensuing 6 months. Participants will be instructed on how to adhere to the TRE protocol. Participants will be evaluated at the Translational Geroscience Laboratory at the end of the protocol, at month 6 (-14/+14 days), when all physiologic assessment will be repeated (Visit 2). If participants terminate the protocol early for any reason, they will be invited to an early termination visit (ETV), which will include repeat physiologic and other evaluations same as in Visit 2. After visit 2, the second fMRI and DXA scan visits will be performed. As stated in the protocol and consent form, MRI and DXA scan visits are optional.

**Power analysis:** Based on our preliminary data analysis, a total of 27 eligible participants will provide 80% power for detecting a decrease of 7.4 in fNIRS against the null hypothesis of no change. A standard deviation of 13.1 was used in the calculation. After adjusting for a 20% dropout, the total of 32 participants will be enrolled. We will use intent-to-treat approach, wherein every participant will be included in the analysis regardless of whether participant is on or off the TRE for the final visit. To control for potential confounding, we will account for BMI, depression, the use of opiates, and other non-exclusive chronic conditions.

**Adherence protocols:** Adherence to study protocol will be monitored using daily surveys of eating periods. All participants will be provided with a fasting diary (electronically or using the sample diary included in supplementary information) in which they will the time that they started and stopped eating each day.

**Dietary intake and physical activity assessments:** Dietary intake data for 24-hour recalls will be collected and analyzed using the Automated Self-Administered 24-hour (ASA24) Dietary Assessment Tool, version 2022, developed by the National Cancer Institute (<https://epi.grants.cancer.gov/asa24>) or using interviewer-led 5-pass USDA method of dietary recall via phone or in-person during visits. The ASA24 system does not capture any personally identifiable data from respondents and respondents' data are protected by industry standard security protocols. The ASA24 tool is validated for use in the general US population and has comparable performance to interviewer-administered 24-h recalls [20]. Participants will complete one 24-h recall biweekly for a total of 12 recalls. Recalls will be scheduled at random to cover different days of the week. Recall data will be used to estimate participants' dietary intake during the intervention. Physical activity level (PAL) will be assessed and classified into sedentary, lightly active, active, and very active using the self-administered CHAMPS Physical Activity Questionnaire for Older Adults. This tool is validated for use in older US adults [21].

**Body composition and physical exam:** Weight and body composition will be acquired using a bioimpedance scale (Tanita Body Composition Analyzer BC-418) at each study visit. Total daily energy expenditure (TDEE) will be estimated using the Mifflin-St. Jeor equation [22-24] multiplied by the appropriate factor according to PAL. Estimated dietary intakes and TDEE will be used to determine whether a participant was in a hypocaloric, eucaloric, or hypercaloric state during the intervention. Moreover, we will collect data on blood pressure and heart rate. Blood glucose and cholesterol will be determined using the Lipid Panel Plus panel from Piccolo Xpress. Optionally, participants may choose to undergo a DXA scan to obtain body composition (% fat mass and % lean mass) and bone density estimates. This medical imaging technique uses low levels of X-rays to measure bone density and body composition. DXA scans will take place at the Oklahoma Shared Clinical and Translational Resources (OKC, OK).

**Study 1: Determine NVC responses using functional near-infrared spectroscopy (fNIRS), electroencephalography (EEG), and dynamic retinal vessel analysis (DVA):**

We will use **fNIRS** recordings to assess NVC responses elicited during the performance of a standardized cognitive n-back test [25]. For the *n-back* task, the participant is required to monitor a series of letters (or numbers) on the computer screen and to respond by clicking the computer mouse right button when the presented letter matches the letter *n*-steps back. We will also record the NVC responses using the fNIRS during standardized motor task, or other standardized stimulation paradigm. We will assess neuronal activity during a similar n-back paradigm (series of numbers) to evaluate the neuronal component of the NVC using the **EEG**.

To directly assess the effect of TRE on NVC responses at the single-vessel level, changes in the diameter of retinal arterioles in response to flickering light stimulation (**DVA**) will be measured, as reported [26]. Static vessel analysis will also be performed right after DVA measures. Functional alterations in retinal arterioles closely correlate with those in cerebral microvessels and predict cognitive impairment [26]. All study participants will be evaluated for visual acuity, using a standard Snellen chart (or similar), and for intraocular blood pressure, using a calibrated Goldmann applanation tonometer or the i-Care device (iCare Ic100 – cleared by FDA to be used in human subjects).

The applanation tonometry procedure involves the use of tetracaine hydrochloride eye drop (or similar) to anesthetize the eye, of instilling fluorescein dye in the conjunctival sac and placing a sterilized prism against the cornea. The tonometer tip will be sterilized before each measurement.

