- The strong magnetic field will affect electronic, magnetic, and metal devices that subjects carry with them or that have been implanted in the subject's body. These will be assessed prior to scanning, and the session will be cancelled if safety criteria are not satisfied.
- Claustrophobia: Some subjects may get anxious in confined spaces.
- Peripheral Nerve Stimulation effects: Occasionally, some subjects may experience muscle twitching or paresthesias, especially in the torso.
- Dizziness: Some individuals may experience light-headedness while in the scanner or when rising from the MRI gurney too rapidly.
- Hearing: MRI scanning produces a loud high frequency tone that can cause hearing damage if appropriate hearing protection is not used. Regarding acoustic noise associated with MRI, all the subjects scanned will receive ear protection (earplugs and/or headphones).

If the subject is not eligible for an MRI at the time of the study, we will not perform this assessment as MRI is not required for study eligibility and it is only used as a secondary outcome.

DXA scans use a minimal amount of radiation (lower than a standard X-ray) and pose no more than minimal risk.

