**M. Statistical Methods**

There are currently no published data available on the effect of TRE on NVC responses in healthy young and older adults. Data obtained from this project will be used as preliminary data for an NIH application.

*Functional near infrared spectroscopy and dynamic retinal vessel analysis:* fNIRS data will be analyzed using a pipeline based on General Linear Model (GLM) approach created using the Brain AnalyzIR toolbox. After conversion of optical densities to change of hemoglobin concentration using the Beer-Lambert law, pre-whitening of data with an autoregressive model-based algorithm, and a discrete cosine transformation using high-pass filter, design matrices will be convolved with a canonical hemodynamic response function to predict brain activation. Parameter estimates (beta-weights), scaling the predictors, will be then used for group level statistics. Group level statistics will be performed using a repeated measures mixed effects model. The model will be defined in a Wilkinson-Rogers formula of 'beta ~ -1 + Group +(1|Subject)'. Output of the mixed effects model statistics will be used for a t test. Increased activation/NVC responses will be considered significant where false discovery rate corrected  $q < 0.05$ . When appropriate, beta values from corresponding channels to the cognitive task will be summarized using mean ( $\pm$ SEM) by group and study visit. We will use repeated measures mixed effects models (with a random subject effect) to assess the main effect of group (TRE vs. control) on NVC responses.

For DVA analysis, each participant will be evaluated for mean maximal arteriolar dilation and mean maximal venular dilation in response to flicker light stimulation. The statistical mean of 3 consecutive examinations will be calculated for each subject and each evaluated parameter as previously described. Data will be summarized using mean ( $\pm$ SEM) by group and study visit. We will use GLM with control and TRE treatment as between-group factor, and Visit 1 and Visit 2 as repeated measures (within group) factor. For post-hoc analysis, we will perform the Bonferroni test. The level of significance will be regarded as  $p < 0.05$ .

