For EEG analysis, the power spectral density of EEG records (obtain during n-back stimulation) will be estimated using the Welch's method and then averaged across 14 channels of the Emotive EPOC research instrument. Spectra will be plotted in a semilogarithmic graph as a function of EEG frequency. For channel-wise comparison, Lilliefors tests will be applied to verify normality of the data. For normally distributed data,  $F$  test will be then used to confirm equality of variances between groups, and the two-sample  $t$  test or the Welch-corrected  $t$  test will be applied for equal or unequal variances, respectively. For not normally distributed data, a Mann-Whitney  $U$  test will be used for group comparison. The false discovery rate (FDR) method of Benjamini and Hochberga will be applied to control for multiple comparisons.

*Peripheral endothelial function:* For analysis of micro- and macrovascular endothelial function, all data will be corrected for mean arterial pressure. Laser speckle data will be normalized to an average of 3 measurements of skin temperature taken before the start of the assessment. For microvascular endothelial function, we will evaluate the maximal perfusion over the baseline perfusion (x-fold change) and the acute

reperfusion index (over the first 4 seconds of cuff release) in the nailbeds and the hand as previously described. For macrovascular endothelial function, change in the brachial artery diameter over the baseline will be calculated (% change), as previously described. When appropriate, data will be summarized using mean ( $\pm$ SEM) by group and study visit. We will use GLM for between-group factor and repeated measures (within group) factor. For post-hoc analysis, we will perform the Bonferroni test. The level of significance will be regarded as  $p < 0.05$ .

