**Cognitive performance:** For cognitive assessment, all NIH Toolbox tests will be organized into two groups of fluid abilities (i.e., working memory, processing speed, episodic memory, and two aspects of executive functioning) and crystallized abilities (i.e., dependent upon past learning and experience), resulting in Standard Scores for these superordinate categories, as well as a total Composite score of all tests. We will use Standard Scores and Composite scores for analysis. These norms were previously reported to align with the age-corrected normative data for the traditional neuropsychological measures, and also because the time interval between baseline Visit 1 and final Visit 2 would not be affected by the participant's race/ethnicity or educational level. We will use GLM for between-group factor and repeated measures (within group) factor. For post-hoc analysis, we will perform the Bonferroni test. The level of significance will be regarded as  $p < 0.05$ .

**Functional magnetic resonance imaging (fMRI)** will be used to quantify patterns of activation associated with brain networks reorganization before and after treatment on each participant. Structural and functional imaging data will be acquired. Structural T1-weighted scans, T2 scans, and scans assessing tissue characterization will be acquired. Functional scans will be acquired with a single-shot EPI sequence. Functional runs will be collected using a cognitive performance task such as the N-back task, and will have a duration of 21 minutes or less. Each MRI session will be less than 2 hours within the magnet. A repeated measures design (baseline and post-TRE) will be conducted for each participant. Additional baseline data will be obtained for secondary correlations. Besides that, a sensitivity analysis testing the comparison of post-TRE only will be additionally conducted.

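### The primary hypothesis joins NVC and endothelial function across at least six separately tested measures, without naming a deciding measure or a rule for combining them, and the stated power covers fNIRS alone

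*Protocol*

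**What the plan says.** Section D (Clinical trial design) gives one primary hypothesis with two parts: "We will test the primary hypothesis that TRE improves NVC responses and endothelial function in older adults".

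Each part is measured in several ways. For the first, Section A states "Study 1 will evaluate NVC responses using functional near-infrared spectroscopy (fNIRS), electroencephalography (EEG), and dynamic retinal vessel analysis (DVA". For the second, Sections A and D use laser speckle imaging and flow-mediated dilation (FMD).

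Section M then sets the tests one domain at a time:

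- **fNIRS:** "Increased activation/NVC responses will be considered significant where false discovery rate corrected" q falls below 0.05.
- **Retinal vessel analysis (DVA):** "each participant will be evaluated for mean maximal arteriolar dilation and mean maximal venular dilation in response to flicker light stimulation", tested at p<0.05.
- **EEG:** a Benjamini-Hochberg correction within the EEG comparisons.
- **Peripheral endothelial function:** for laser speckle, "we will evaluate the maximal perfusion over the baseline perfusion (x-fold change) and the acute" reperfusion index; for FMD, percent change in diameter. The level is again p<0.05.
- **Cognition:** "We will use Standard Scores and Composite scores for analysis", again at p<0.05. Cognition is not part of the primary hypothesis.

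For DVA, endothelial function and cognition, Section M adds "For post-hoc analysis, we will perform the Bonferroni test".

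The only outcome given a rank is MRI, of which Section K says "it is only used as a secondary outcome"; the note under the eligibility table in Section H says the same of fMRI. The power analysis in Section D uses fNIRS alone: 27 participants, a change of 7.4, SD 13.1, 80% power.

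**The concern.** A primary hypothesis is confirmed or not by a stated rule, and here the rule is missing at two levels. No measure is named as deciding for either construct, and nothing says how the two constructs combine.

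The existing corrections do not fill the gap. The false discovery rate steps work within fNIRS and within EEG. The Bonferroni step is a post-hoc test inside each model. None of them acts across measures.

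Two things are at stake. First, if fNIRS is null and FMD is positive, or the reverse, the protocol does not settle what may be concluded, and the choice could be made after the data are seen. Second, the sample size was worked out for one test on one modality, while the hypothesis it is meant to serve has two parts.

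**Working it through.** **Inputs from the protocol.** Section D: n=27 evaluable, change 7.4, SD 13.1, 80% power. Section M: six measures that bear on the primary hypothesis, namely fNIRS activation (1), DVA arteriolar and venular dilation (2), laser speckle maximal perfusion and acute reperfusion index (2), and FMD (1). EEG, and separate testing of nailbeds and hand, would add to the count and are left out.

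**Assumptions.** Two-sided 0.05 (the power statement gives no level). A paired test of Visit 2 against Visit 1 for each measure, since Section D has every participant follow TRE. fNIRS counted as one test at 5%, which is what false discovery rate control at 0.05 gives when nothing is truly changed. A common correlation between measures of 0 to 0.8, because the protocol gives none.

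**Step 1: reproduce the stated power.** Standardized effect = 7.4/13.1 = 0.565. Paired t test with 26 degrees of freedom, noncentrality 0.565 × √27 = 2.94: power is 80.7% at n=27 and 79.1% at n=26. The stated 27 for 80% is therefore right, for one fNIRS test.

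**Step 2: any one measure is enough.** With independent measures, the chance of at least one false positive is 1 − 0.95^6 = 26.5%. For improvement only, at 2.5% per measure, it is 1 − 0.975^6 = 14.1%. Simulation with n=27 and no true effect:

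| Correlation | At least one false positive | At least one false improvement |
|---|---|---|
| 0 | 26% | 14% |
| 0.3 | 24% | 12% |
| 0.5 | 21% | 11% |
| 0.8 | 14% | 7% |

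One named test would give 5% and 2.5%.

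**Step 3: both constructs must be positive.** Take the most lenient version: at least one of three measures significant in each construct. Under independence the error is (1 − 0.95^3)^2 = 0.1426^2 = 2.0%. By simulation it is about 3% at correlation 0.3, 4% at 0.5 and 6% at 0.8. False-positive error is not the problem under this reading.

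**Step 4: power when both are required.** If fNIRS and one endothelial measure must both be significant, joint power cannot exceed the 80.7% for fNIRS. The protocol gives no endothelial effect or SD. If the endothelial effect were also 0.565 SD, joint power would be 0.807^2 = 65% under independence, then 67%, 70% and 73% at correlations 0.3, 0.5 and 0.8. The result depends heavily on that assumed effect. Under independence, an endothelial effect of 0.3 SD gives 0.324 × 0.807 = 26%, and 0.8 SD gives 0.979 × 0.807 = 79%.

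**The case against.** **The hypothesis says that both improve, so the false-positive rate is low.** This is the strongest objection, and it stands as far as it goes. A reader might infer that the plan carries a false-positive risk of a fifth to a quarter as a matter of fact. The documents do not support that: the figure needs an any-one-measure rule that the protocol does not state, and on the literal reading the error is about 2-6%. But the protocol does not state the both-required rule either, and under it the 80% power no longer describes the hypothesis. One of the two defects remains whichever reading is chosen.

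**fNIRS is the only powered measure, so it is primary in effect.** That is a natural guess, but Section D does not say it, and its hypothesis includes endothelial function, which fNIRS does not measure here. If fNIRS is what was meant, one sentence cures the point.

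**Multiplicity is commonly left to an analysis plan, and this is a preliminary study.** Section M does describe the data as groundwork for a grant application, and strict error control across mechanistic measures in 32 people is a matter of judgement. This limits the severity. It does not remove the point, because the protocol itself fixes a two-part primary hypothesis, the separate thresholds and a sample size that fits only one part.

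**The simulated tests are not those written.** Section M specifies models with a control group that Section D does not provide. Paired tests follow Section D. The group factor would change the number of post-hoc comparisons within a model, but would still give no control across measures.

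**Conclusion.** The point holds as a missing decision rule, together with a power statement that does not match the hypothesis. It does not hold as a single inflated error rate.

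- **If any one measure suffices:** about 14-26% for at least one false positive, and about 7-14% for a false claim of improvement. Both rest on six measures, n=27, paired tests and correlation 0.8 to 0.
- **If both constructs are required:** error of about 2-6%. Power is at most the 80.7% for fNIRS, and about 65-73% only if the endothelial effect equals the fNIRS effect.

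A reader might take 65-73% as the trial's true power. It is not: the protocol gives no endothelial effect, and other plausible effects move joint power widely. The sponsor should act, but given the preliminary purpose this is a correction that should be made rather than a reason to stop.

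**What to change.** **Preferred.** In Section D, name one primary contrast: the Visit 2 minus Visit 1 change in one pre-specified fNIRS n-back summary value per person, tested once at two-sided 0.05. Reword the primary hypothesis to NVC responses measured by fNIRS. State the expected direction as well, since the power statement refers to a decrease while the fNIRS rule in Section M refers to increased activation. In Section M, state that all other NVC, endothelial and cognitive measures are secondary or exploratory, are reported with estimates and 95% confidence intervals, and cannot on their own confirm the primary hypothesis. Any ordering of the secondary measures is for the sponsor to choose.

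**If the two-part hypothesis is kept.** Name one endothelial measure and require both it and fNIRS to be significant. State that the 80% applies to fNIRS alone, and recalculate the joint power from a justified endothelial effect and SD.

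**Cost.** The preferred option is a wording change in Sections D and M, with no added participants, visits or measurements. A positive result on another measure alone could then no longer be claimed as confirming the primary hypothesis. Keeping both parts may call for a larger sample if joint power of 80% is wanted.

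### Section D and the sample size describe one TRE arm, but Section M and Aim 2 specify TRE-versus-control comparisons, so the fNIRS and EEG analyses as written cannot test change on TRE

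*Protocol*

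**What the plan says.** **Design and sample size (Protocol Section D).** After baseline, "all participants will be instructed to maintain TRE for the ensuing 6 months". Assessments are repeated at month 6. No randomisation, control condition, control recruitment or control sample size is described. The power analysis tests a change of 7.4 in fNIRS, SD 13.1, against no change, with 27 evaluable and 32 enrolled.

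**Analysis (Protocol Section M).**
- fNIRS: a mixed model whose only fixed term is Group, with a random subject effect. The stated purpose is "to assess the main effect of group (TRE vs. control) on NVC responses".
- DVA: "We will use GLM with control and TRE treatment as between-group factor", with Visit 1 and Visit 2 as the within-group factor.
- EEG: an F test "used to confirm equality of variances between groups", then a two-sample t, Welch or Mann-Whitney test. No paired test and no visit term is given.
- Peripheral endothelial function, and in the same words cognition: "We will use GLM for between-group factor and repeated measures (within group) factor".
- fMRI: a within-participant comparison of baseline with post-TRE. In addition, "a sensitivity analysis testing the comparison of post-TRE only will be additionally conducted".

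**Elsewhere.** Aim 2 (Section A) treats cells with "fasting serum obtained from older adults undergoing TRE and age-matched controls". Section I speaks of enrolment into each group, and Section O gives example data labels for both control and TRE participants.

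**The concern.** The protocol carries two designs. Recruitment, treatment and sample size follow a single-arm before-after study. Most of the analysis section follows a controlled comparison. If the trial runs as Section D describes, the group factor has one level and the contrasts built on it do not exist. Analysts would then have to choose the fNIRS and EEG models after seeing data, or bring in outside controls, who would be non-randomised and not covered by the sample size.

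Interpretation is also affected. The aims are worded as determining the impact of TRE. Without a comparator, a six-month change also contains practice on the repeated n-back and NIH Toolbox tests, time trends and regression to the mean.

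**Working it through.** **1. Which design does the sample size belong to?**

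Inputs from Section D: difference 7.4, SD 13.1, 27 evaluable, 80% power. Alpha and sidedness are not stated there. Two-sided 0.05 is assumed; Section M uses p < 0.05 for DVA.

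Standardised effect: 7.4 / 13.1 = 0.565.

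Paired or one-sample t-test, noncentrality 0.565 × √n:
- n = 26: power 79.1%
- n = 27: power 80.7%, so 27 is the smallest n that reaches 80%

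Other readings tried:

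| Test | n for 80% power |
|---|---|
| One-sample z, two-sided | 25 |
| One-sample t, one-sided | 21 |
| One-sample z, one-sided | 20 |
| Two-sample z, two-sided | 50 per arm |
| Two-sample t, two-sided | 51 per arm |
| Two-sample z, one-sided | 39 per arm |

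Of these, only the two-sided paired or one-sample t-test returns 27. This implies that 13.1 was used as the SD of change, which the protocol does not say. The trial was sized without a control group.

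**2. What remains of each Section M analysis with one arm?**

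| Outcome | Stated analysis | With one arm |
|---|---|---|
| fNIRS (powered) | Group as only fixed term, subject random | One mean beta: tests task activation, not change on TRE |
| EEG | Two-sample tests | No second sample, so no usable test |
| DVA | Group × visit GLM | Group and group-by-visit lost; visit contrast remains |
| Endothelial function | Between-group and within-group factors | As for DVA |
| Cognition | Between-group and within-group factors | As for DVA |
| fMRI | Within-participant pre/post | Estimable as written |

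Five of the six outcome analyses refer to a between-group comparison. For two of them (fNIRS and EEG) nothing in the stated model or test addresses change from Visit 1 to Visit 2. The Aim 2 serum comparison also needs a second group. A within-person alternative is available, because Section F has blood collected at both visits.

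**3. If a concurrent control group were intended (illustration only)**

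Take 7.4 as the between-group difference and 13.1 as the SD of change; the protocol states neither.
- Required per arm: 2 × (1.960 + 0.842)² × (13.1/7.4)² ≈ 49.2, so 50 (51 with the t distribution). That is 100 to 102 evaluable, or 100/0.8 = 125 to 102/0.8 = 127.5, i.e. 128, enrolled.
- Power if the 32 were split 16/16: noncentrality 0.565 × √(16/2) = 1.60 on 30 df, about 34%.

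**The case against.** The best case on the other side is that this is a small single-arm study whose analysis text carries some surplus wording. Section M calls its data preliminary for a grant application, an uncontrolled pilot is a legitimate choice, and Study 2 in Section D is explicitly before-and-after. Much of that stands, and it limits the point in several ways.

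- A reader might infer that most planned tests cannot be run. The documents do not support that. The DVA, endothelial and cognitive models carry a within-group visit factor that can be estimated once group is removed, and fMRI is within-participant already.
- A reader might take it as settled that no controls will ever be enrolled. Section D and the power statement favour that reading, but Sections I and O refer to groups and control labels. The document contradicts itself on this.
- A reader might count the fMRI post-TRE-only sensitivity analysis as another control comparison. The sentence names no comparator, so it supports only a request for clarification.
- A reader might take 34% as the power of this trial. It describes a 1:1 split that the protocol does not propose.

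Two defences do not succeed. One is that Group in the fNIRS formula could be read as a visit label; the same paragraph defines group as TRE versus control. The other is that the covariates listed in Section D (such as BMI, depression and opiate use) deal with confounding. Stable characteristics already cancel in a within-person contrast, and adjustment cannot supply a missing comparator. Nor can the matter be left to a statistical analysis plan, because the protocol itself states both versions and the choice between them determines recruitment and sample size.

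**Conclusion.** The contradiction is real and must be fixed, because it reaches the outcome that sized the trial. The power statement tests no change in fNIRS, while the stated fNIRS model contains no term for change. EEG has no test that can be run in one arm. In DVA, endothelial function and cognition the fault is confined to the group and group-by-visit terms. In Aim 2 the comparator serum has no described source.

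The finding that the sample size is single-arm rests on two-sided 0.05 and on 13.1 being the SD of change. The contradiction between sections rests on neither. The limit on causal wording follows from having no comparator; the documents give no figure for practice or time effects, so their size is unknown. It is a matter of interpretation and not an objection to running a single-arm study.

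**What to change.** First, state which design is intended and reconcile Sections A, D, I, M and O with it.

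**If single-arm, as the power statement supports:**
- fNIRS and EEG: replace Group with Visit as fixed effect and Subject as random effect, or use paired tests.
- DVA, endothelial function and cognition: drop the between-group factor and keep visit.
- Report the mean Visit 2 minus Visit 1 change with 95% CI for each endpoint.
- Study 4: use each participant's own Visit 1 serum as comparator for Visit 2 serum.
- Remove the control and group wording in Aim 2, Section I and Section O.
- Say what the fMRI post-TRE-only analysis compares.
- Word aims and conclusions as change during TRE, and name practice and time effects as alternative explanations.

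This needs no new data or participants. The 27 evaluable and 80% power continue to apply. The cost is a wording amendment and more modest conclusions.

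**If a concurrent control group is intended:** Section D must describe its allocation and recruitment, and the power statement must be redone for a between-group test. That is not a wording change. Under the illustrative assumptions above it means about 125 to 128 enrolled instead of 32.
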